## Abstract

**Introduction::**

While the role of early mobilization in the immediate postinfarction period has been well demonstrated, little is known in present about the link between early mobilization and reduction of systemic inflammation. At the same time, the impact of early mobilization on regression of left ventricular remodeling has not been elucidated so far.

**Material and methods::**

Here we present the study protocol of the REHAB trial, a clinical descriptive, prospective study, conducted in a single-center, with the purpose to analyze the impact of early mobilization in reducing left ventricular remodeling, the complication rates and mortality in patients who had suffered a recent acute myocardial infarction (AMI). At the same time, the study aims to demonstrate the contribution of early mobilization to reduction of systemic inflammation, thus reducing the inflammation-mediated ventricular remodeling. 100 patients with AMI in the last 12 hours, and successful revascularization of the culprit artery within the first 12 hours after the onset of symptoms in ST-segment elevation acute myocardial infarction or within first 48 hours in non ST-segment elevation AMI will be enrolled in the study. Based on the moment of mobilization after AMI patients will be distributed in 2 groups: group 1 – patients with early mobilization (<2 days after the onset of symptoms) and; group 2 – subjects with delayed mobilization after AMI (>2 days after the onset of symptoms). Study outcomes will consist in the impact of early mobilization after AMI on the ventricular remodeling in the post-infarction period, as assessed by cardiac magnetic resonance imaging, the rate of in-hospital mortality, the rate of repeated revascularization or MACE and the effect of early mobilization on systemic inflammation in the immediate postinfarction phase.

**Conclusion::**

In conclusion, REHAB will be the first trial that will elucidate the impact of early mobilization in the first period after AMI, as a first step of a complex cardiac rehabilitation program, to reduce systemic inflammation and prevent deleterious ventricular remodeling in patients who suffered a recent AMI.

## Introduction

1

### Background and rationale

1.1

As a severe form of coronary heart disease, acute myocardial infarction (AMI) involves a significant burden in terms of disability, especially in the increasing population of elderly patients.^[1,2]^ Impressive progress of diagnostic and therapeutic procedures in the last years significantly reduced the AMI-related mortality. As a consequence, rehabilitation of AMI survivors has become a real public health issue and a major challenge to be solved.^[3,4]^ In this context, both health care systems and general population have started to become aware of the fact that the current approach, mainly involving interventional and pharmacological treatments, is neither effective nor sufficient.^[5,6]^ As patients with recent AMI deserve special attention, structured multifaced and multidisciplinary interventions for assessment and management of cardiovascular (CV) risk factors, guidance on physical activity and psychosocial sustenance^[7,8]^ were developed and implemented as case-management models of cardiac rehabilitation (CR) programs.^[9–11]^

Divided in 3 phases: inpatient, outpatient, and long-term interventions, CR aims to improve functional capacity and recovery, prevent disability and restore the quality of life.^[12]^ Along with patient physical reintegration, CR programs involve preventive strategies for subsequent CV events, death or hospitalization from cardiac causes.^[13]^ While the objectives are identical, settings differ according to local or national protocols and experiences, including residential, ambulatory community, or home-based strategies.^[14]^

One of the most important predictors of long-term evolution after an AMI is represented by the left ventricular (LV) remodeling. Postinfarction LV represents a maladaptive and dynamic process resulting from the complex interaction between the size of the infarcted area, genetic predisposition and inflammation, in which systemic inflammation plays a crucial role. This phenomenon is associated with mechanical and biochemical changes, leading to arrhythmia, ventricular dysfunction and heart failure on the long term.^[15–18]^ A large variety of biomarkers have proven their prognostic role in LV remodeling, being well associated with inflammation and microcirculatory dysfunction (NT-proB-type natriuretic peptide, high-sensitive cardiac troponin T, aspartate aminotransferase, alanine aminotransferase, high sensitive C-reactive protein [hs-CRP], and lactate dehydrogenase).^[19]^

Among inflammatory biomarkers whose maintenance at a high serum level has been proved to be prognostic for ventricular remodeling, interleukin-6 (IL-6), tumor necrosis factor-α, and interleukin-1β are the most widely studied, and may serve as prognostic markers for the development of postinfarction heart failure. At the same time, it has been hypothesized that specific CD11/CD18 integrin receptors, complement cascade activators, complement component 1, complement component 5 or P-selectin can be used to form antibodies that would block the inflammation, however the results of such studies are still un-conclusive.^[20–23]^

In a series of non-pharmacological therapeutic strategies concerning the inflammatory component of atherosclerotic disease, exercise training proved to be the most outstanding.^[24]^ The success of regular exercise in reducing the risk of coronary disease development and complications was strongly associated with the reduction of C-reactive protein (CRP) and fibrinogen levels.^[25]^ Moreover, Church et al found an inverse correlation between cardiorespiratory exercise and systemic level of CRP, an inflammation-related biomarker validated as a significant predictor for the development of an AMI.^[25,26]^

According to current ESC and ACC/AHA guidelines for the management of patients with ST-segment elevation acute myocardial infarction (STEMI), mobilization should be performed in the first 12 and 24 hours following an uncomplicated acute AMI (level of evidence C).^[26,27]^ While the role of early mobilization in the immediate postinfarction period has been well demonstrated, little is known in present about the link between early mobilization and reduction of systemic inflammation. At the same time, the impact of early mobilization on regression of LV remodeling has not been elucidated so far.

### Study objectives

1.2

The *primary objective* of the study is to evaluate the impact of early mobilization after AMI on the ventricular remodeling in the post-infarction period, as assessed by cardiac magnetic resonance (CMR) imaging.

The *secondary objectives* include

(1)to investigate the effect of early mobilization on systemic inflammation in the immediate postinfarction phase(2)to investigate the impact of early mobilization on in-hospital mortality and the role of early mobilization in reducing in-hospital complications in patients suffering an AMI.

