### Study timeline

2.7

REHAB study will be conducted from October 2019 to October 2020.

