### Outcomes

2.8

The *primary outcome* of the study will consist in the impact of early mobilization after AMI on the ventricular remodeling in the post-infarction period, as assessed by CMR imaging.

*Secondary outcomes* of the study will be represented by rate of in-hospital mortality and the rate of repeated revascularization or MACE (including CV death or stroke) in patients with early mobilization as compared to those with delayed mobilization, and the effect of early mobilization on systemic inflammation in the immediate postinfarction phase.

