### Participation timeline

2.9

Baseline (day 0):

Achieve written informed consent form all patients.Check all inclusion/exclusion criteria.Record demographic information, medical records, CV risk factorsPerform and record physical examination and 12-lead electrocardiography (ECG).Laboratory analysis (CBC, routine biochemistry, inflammatory biomarkers, acute adhesion molecules).Transthoracic echocardiography / speckle tracking.

Visit 1 (day 7 / discharge from the hospital):

hs-CRP assessment.

Visit 2 (month 1):

LGE-CMR (myocardial fibrosis/scar, infarct size, transmurality, remodeling).

Visit 3,4,5 (month 3,6,9)

Record results of physical exam, medical records, ECG.Transthoracic echocardiography / speckle tracking.

Final study visit (month 12)

Record results of physical exam, medical records, ECG.Transthoracic echocardiography / speckle tracking.End-point assessment.

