### Sample size

2.10

The study will enroll 100 patients with AMI who presented within the first 12 hours after the onset of symptoms and underwent successful revascularization of the culprit artery within the recommended timeframe, with TIMI 3 flow. Patients will be divided into 2 groups on the basis of the time interval from admission to mobilization: early (<2 days) mobilization group, versus delayed (>2 days) mobilization group. The sample size was calculated using Stat Mate 2.0 software, which indicated that a sample size of 50 subjects per group has a 90% power to detect an increase in major adverse CV events rates proportion of 3.28, with a significance level (alpha) of 0.05 (2-tailed).

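### The event objective covers the hospital stay, but MACE has no stated window, end-points are assessed at month 12, and the 90% power for MACE names neither a period nor group rates

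*Protocol article*

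**What the plan says.** Four sections of the protocol article bear on the event outcome.

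- **1.2 Study objectives.** The event part of the secondary objectives is in-hospital mortality and "the role of early mobilization in reducing in-hospital complications in patients suffering an AMI". The window is the hospital stay.
- **2.8 Outcomes.** The event outcomes are the "rate of in-hospital mortality and the rate of repeated revascularization or MACE (including CV death or stroke"). Mortality carries the in-hospital limit. The second item starts afresh with its own rate and has no window. The abstract has the same structure.
- **2.9 Participation timeline.** At "Visit 1 (day 7 / discharge from the hospital") the only listed item is hs-CRP. The entry "End-point assessment" appears once, under "Final study visit (month 12").
- **2.10 Sample size.** The only power statement in the document is 90% power with 50 per group, two-sided alpha 0.05, for an "increase in major adverse CV events rates proportion of 3.28". It gives no group rates and no period over which they apply.

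The study calendar in 2.7 also matters: "REHAB study will be conducted from October 2019 to October 2020".

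**The concern.** For complications and MACE, the objective points to the hospital stay and the visit schedule points to month 12. The outcome list and the sample-size paragraph settle on neither. An analysis plan could choose a window, but either 1.2 or 2.9 would still read differently from that choice, so this is a conflict between stated sections and not only an omitted detail.

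Two things are at stake. First, an in-hospital comparison and a 12-month comparison answer different questions, and the article's text can be cited for either. Second, 2.10 justifies the sample size by MACE alone. Power for a binary outcome depends on the event rates, and the rates depend on how long events are counted. Until the window is fixed, the 90% describes no identifiable comparison.

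**Working it through.** **Step 1: the sections side by side**

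| Item | 1.2 | 2.8 | 2.9 | 2.10 |
|---|---|---|---|---|
| Mortality | in hospital | in hospital | no separate entry | not used |
| Complications | in hospital | not named as such | no separate entry | not used |
| Repeat revascularization or MACE | not named | no window | end-points at month 12 | MACE only; no period |

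Mortality agrees between 1.2 and 2.8. The second and third rows do not line up.

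**Step 2: can the stated 90% be reproduced?**

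Inputs from 2.10: n = 50 per group, two-sided alpha 0.05, effect 3.28. The base rate and the scale of 3.28 are not given, so the figure cannot be reproduced directly. What can be shown is how far it depends on them.

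Read 3.28 as a risk ratio, so p2 = 3.28 × p1, where p1 is the rate in the lower-rate group. The normal-approximation power is

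power = Φ[(p2 − p1 − 1.96 × SE0) / SE1],

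with SE0 = √(2 p̄(1 − p̄)/50), p̄ = (p1 + p2)/2, and SE1 = √((p1(1 − p1) + p2(1 − p2))/50).

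Worked example at an assumed p1 = 5%:
- p2 = 16.4% and p̄ = 10.7%
- SE0 = 0.0618 and SE1 = 0.0608
- (0.114 − 1.96 × 0.0618)/0.0608 = −0.12, so power = 0.45

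The same calculation at other base rates, all of them assumptions:

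| p1 | p2 | Power | Power, Fisher's exact test | Expected events, 50 × (p1 + p2) |
|---|---|---|---|---|
| 2% | 6.6% | 0.20 | 0.045 | 4.3 |
| 5% | 16.4% | 0.45 | 0.31 | 10.7 |
| 10% | 32.8% | 0.80 | 0.75 | 21.4 |
| 12.2% | 40.2% | 0.90 | 0.87 | 26.2 |

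On this reading the stated 90% is met at about 12% versus 40%. With a continuity correction the pair is about 13.5% versus 44.1%. For 90% power, the size per group would be 412 at a base rate of 2%, 153 at 5% and 66 at 10%.

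**Step 3: other readings of 3.28**

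- Odds ratio: power never exceeds about 83% at any base rate.
- Difference of 3.28 percentage points: at most about 25%.
- Absolute difference of 0.328: about 99% at a base rate of 2%, 94% at 20% and 92% at 33.6%.
- Hazard ratio: about 30 events (Schoenfeld) or 38 events (Freedman) are needed for 90% power.

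Power therefore runs from well below 90% to above it, depending on two things that 2.10 does not state.

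**Step 4: can month 12 be reached?**

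The calendar in 2.7 spans 12 months. If it covers both enrolment and follow-up, a patient enrolled k months after the start has at most 12 − k months of follow-up. Only patients enrolled at the very start could attend a month-12 visit. A simple 12-month proportion would then be missing for almost everyone enrolled later.

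**The case against.** The natural defence is that MACE is meant to run to month 12, because that is where 2.9 puts end-point assessment, and that 1.2 is merely worded too narrowly. The abstract and section 3 support this: they state the purpose as complication rates and mortality with no in-hospital limit. Section 1.2 also introduces its list in a way that need not be exhaustive. This is a fair reading and may be what was intended. It still leaves 1.2 to be reworded, 2.8 and 2.10 without a period, and a month-12 window that the calendar hardly allows.

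One could instead stretch the in-hospital limit in 2.8 to cover MACE. The sentence structure argues against it, and 2.9 would then lack event recording at discharge.

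Three stronger readings may tempt a reader, and the document does not support them.

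- *That no outcome measures the in-hospital objective.* In-hospital mortality appears in both 1.2 and 2.8 with the same window. Revascularization and stroke may also be how complications are measured; what they lack is a window.
- *That leaving reinfarction unnamed is an error.* The MACE list is open-ended, and component definitions commonly belong in the full protocol.
- *That the 90% is false.* This needs both an assumed base rate and a risk-ratio reading. An absolute difference of 0.328 gives more than 90% power at every base rate tried.

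Nor can one say that the window will be chosen after the data are seen, since an analysis plan that is not shown may fix it.

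**Conclusion.** The conflict stands in a limited form. For complications and MACE, 1.2 and 2.9 point to different windows, and 2.8 and 2.10 give none. In-hospital mortality is unaffected.

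The effect on power is illustrative only. If 3.28 is a risk ratio, power with 50 per group is about 20% to 45% at assumed lower-group rates of 2% to 5%, and it reaches 90% at about 12% versus 40%. The document supplies neither the base rate nor the scale, so the claim can be neither confirmed nor refuted, and no corrected sample size can be derived. The unclear scale of 3.28 is a separate weakness that fixing the window alone would not cure.

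The point should be corrected. It concerns a secondary outcome, but that outcome carries the only sample-size justification in the article.

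**What to change.** 1. State one MACE definition and one window, and use them in 1.2, 2.8, 2.9 and 2.10. Which window to use is for the investigators to decide.
2. If the window is 12 months, analyse time to first event with censoring, because the calendar in 2.7 cannot give full follow-up under staggered enrolment. Report in-hospital events separately as counts with confidence intervals.
3. Start the group comparison at a 2-day landmark and not at symptom onset. Section 2.5 defines the groups by mobilization before or after 2 days, so an event in those days can itself decide the group. Report earlier events separately. Section 2.5 counts the 2 days from symptom onset and 2.10 from admission, so the landmark needs one stated origin.
4. Restate 2.10 with both group rates over the chosen window, the scale of the effect, and the resulting power.
5. List event recording at the discharge visit in 2.9, where only hs-CRP now appears.

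The cost is mostly wording, plus one added item at discharge. Events in the first 2 days leave the group comparison, and the restated power may be lower than 90%.

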## Methods/design

2

### Study design

2.1

This is a prospective, non-randomized, cohort study, carried out in a single-center, which aims to assess the link between early mobilization after AMI, systemic inflammation, and LV remodeling in patients with recent STEMI.

### Ethics approval

2.2

The clinical study has the approval of the local Ethics Committee for Scientific Research of the University of Medicine and Pharmacy of Tirgu-Mures (certificate of approval: 348/13.12.2017) and the Ethics Committee for Scientific Research of the Cardio Med Medical Center (certificate of approval: 30/28.12.2017). All study procedures will be conducted according to the Declaration of Helsinki and each subject will provide signed written informed consent before randomization process.

### Study population

2.3

The study will be a single-center, observational, non-randomized study including 100 patients with AMI, presenting with either STEMI or non ST-segment elevation AMI (NSTEMI).

Inclusion criteria:

Patients with AMI in the last 12 hours.Successful revascularization of the culprit artery within the first 12 hours after the onset of symptoms in STEMI or within first 48 hours in NSTEMI (according to the risk class).Signed written informed consent.

Exclusion criteria:

Patient refusal;Any condition that would contraindicate CMR examination;Women during pregnancy or lactation period;Women able to procreate without any contraceptive usage;Chronic kidney disease (glomerular filtration rate <60 ml/min/1.73m^2^) or acute renal injury that requires hemodialysis;Any type of neoplasia documented in the last 3 years before randomization;Expectation of life <1 year.

### Study settings

2.4

The study will be carried out in the Center of Advanced Research in Multimodality Cardiac Imaging of the Cardio Med Medical Center, in Targu Mures, Romania, and funding will be provided by the European Union and the Government of Romania through the Ministry of European Funds, accessed via research grant number 103545/2016 - “High performance multimodal MRI/CT imaging platform, for applications in computational medicine, nanoparticles and hybrid imaging for the research of atherothrombotic disorders - CARDIO IMAGE” - (contract number 43/05.09.2016).

### Study groups

2.5

This study will enroll 100 patients with AMI meeting the inclusion criteria, who will be distributed in two groups: group 1 – patients with early mobilization (<2 days after the onset of symptoms) and; group 2 – subjects with delayed mobilization after AMI (>2 days after the onset of symptoms).

### Study procedures and outcome assessment

2.6

Medical records, physical exam, laboratory analysis (complete blood count [CBC], biochemistry, serum levels of hs-CRP, matrix metalloproteinase, IL-6, NT-pro-BNP);ElectrocardiographyTransthoracic echocardiography for assessment of LV systolic and diastolic performance, speckle tracking echocardiography, Dobutamine viability testLate gadolinium enhancement CMR for evaluation of ventricular function and remodeling, extent of myocardial scar and transmurality index.

#### Biomarkers assays

2.6.1

Routine biochemistry and CBC analysis will be performed at the main laboratory of the Emergency Clinical County Hospital of Tirgu-Mures, immediately after randomization, during the acute phase of infarction. Inflammatory status (hs-CRP levels) will be evaluated at 7 days after the acute cardiac event via immunoturbidimetric assay. Serum levels of matrix metalloproteinase 9 and IL-6 will be evaluated with enzyme linked immunosorbent assay. Serum inflammatory biomarkers will be analyzed in Advanced Medical and Pharmaceutical Research Center of the University of Medicine and Pharmacy Tirgu-Mures. Serum levels of NT-proBNP will be determined at randomization, at the main laboratory of the Emergency Clinical County Hospital of Tirgu-Mures by electrogenerated chemiluminescence.

#### Transthoracic echocardiography

2.6.2

Transthoracic echocardiographic assessment will be performed at first visit in all patients, in the first days during the hospitalization for the acute coronary event. Speckle tracking technology will be used for evaluation of ventricular volumes and wall motion analysis, using a Vivid E9 ultrasound system (General Electric Vingmed Ultrasound, Horten, Norway).

#### Late gadolinium-enhancement cardiac magnetic resonance (LGE-CMR)

2.6.3

All CMR images will be acquired with the use of a 1.5T Siemens Magnetom Aera equipment. The LGE-CMR will be used to quantify the infarct size, the extent of myocardial necrosis and the transmurality index, 10 minutes after gadolinium intravenous injection. Imaging data post-processing will be conducted with the use of Medis Q Mass 8.1 software (Medis, Leiden, the Netherlands), which involves manually tracing of the epicardial and endocardial borders, while setting the threshold for hyper-enhancement in the acquired image sequence.

### Study timeline

2.7

REHAB study will be conducted from October 2019 to October 2020.

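### The stated study dates (October 2019 to October 2020) leave at most 31 days of enrolment for patients who are to reach the month-12 end-point visit

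*Protocol article*

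**What the plan says.** Study timeline (2.7) is one sentence: "REHAB study will be conducted from October 2019 to October 2020". It does not call this an enrolment period, and the article gives no other start, recruitment or closing date.

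Participation timeline (2.9) sets the visits for each patient: day 0, day 7 or discharge, month 1, then "Visit 3,4,5 (month 3,6,9") and "Final study visit (month 12"). Month 1 carries the only scheduled CMR, "LGE-CMR (myocardial fibrosis/scar, infarct size, transmurality, remodeling"). The last visit carries "Transthoracic echocardiography / speckle tracking.End-point assessment", and end-point assessment is listed at no other visit.

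Study groups (2.5) fixes the number: "This study will enroll 100 patients with AMI meeting the inclusion criteria". Under Study population (2.3) the entry criterion is "Patients with AMI in the last 12 hours", so patients join as they present. Sample size (2.10) rests on MACE: "50 subjects per group has a 90% power to detect an increase in major adverse CV events rates proportion of 3.28".

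**The concern.** A study with staggered entry lasts as long as its enrolment period plus the follow-up of the last patient. Here the stated duration of the whole study is about equal to the follow-up of a single patient, which leaves almost no time for enrolment. Read literally, every patient enrolled after the opening weeks is still under follow-up when the study closes.

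Two things are at stake. First, the month-12 assessment would be missing for administrative reasons in a share of patients that depends on how fast they are enrolled. Second, MACE and repeat revascularization after discharge would be counted over follow-up of unequal length, so simple proportions would mix patients watched for weeks with patients watched for a year. The groups are formed by time of mobilization and not by randomization. If mobilization practice drifted during the year, length of follow-up could differ between the groups and bias the comparison.

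**Working it through.** **Inputs from the protocol article**
- Window: October 2019 to October 2020 (Study timeline).
- Visits: months 1, 3, 6, 9 and 12 after day 0 (Participation timeline).
- Patients: 100, at one centre, enrolled as they present (Study groups, Study population).

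**Assumption.** The article gives no accrual rate. Even accrual is assumed, and the enrolment period is varied.

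**Step 1: room for enrolment.** The last usable enrolment day is the end of the window minus 12 months (366 days, because February 2020 has 29).
- Widest window, 1 October 2019 to 31 October 2020: 397 − 366 = 31 days.
- Mid-October to mid-October: 367 − 366 = 1 day.
- Narrowest window, 31 October 2019 to 1 October 2020: 337 days, shorter than 366, so 0 days.

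For all 100 to reach month 12, all must be enrolled in October 2019: 100 / 31 ≈ 3.2 per day at one centre.

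**Step 2: share reaching month 12.** With a 13-month window and even accrual over A months, the share is (13 − 12)/A = 1/A. Mean follow-up, capped at 12 months, is [12 + 13(A − 1) − (A² − 1)/2]/A.

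| Enrolment period A | Reach month 12, of 100 | Mean follow-up, months |
|---|---|---|
| 3 months | 33 | 34/3 = 11.3 |
| 6 months | 17 | 59.5/6 = 9.9 |
| 12 months | 8 | 83.5/12 = 7.0 |

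At A = 2 the share is one half. Most patients therefore miss month 12 unless enrolment ends within about two months.

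**Step 3: the other visits.** In the 13-month window the share reaching month m is (13 − m)/A, capped at 1.

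| Visit | A = 3 | A = 6 | A = 12 |
|---|---|---|---|
| Month 1 | 100% | 100% | 12/12 = 100% |
| Month 3 | 100% | 100% | 10/12 = 83% |
| Month 6 | 100% | 100% | 7/12 = 58% |
| Month 9 | 100% | 4/6 = 67% | 4/12 = 33% |

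If enrolment instead runs to the last day of the window, the three windows of Step 1 give about 91–92 of 100 at month 1, 73–77 at month 3, 46–54 at month 6, 19–31 at month 9 and 0–8 at month 12.

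**Step 4: duration needed.** Enrolment period plus 12 months. With 12 months of enrolment from October 2019, the last month-12 visit falls about 24 months after the start, in about October 2021.

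**The case against.** The strongest reply is that the dates were meant as the enrolment period, in a condensed article that gives timing one sentence. That is possible, and if so a single corrected sentence settles the matter. But the text speaks of the conduct of the study and nothing else in the article separates enrolment from follow-up. The two sections conflict as written. They therefore have to be reconciled, but the conflict does not show that data will be lost.

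The second reply is that the outcomes that matter most are safe. Much of this stands. The primary outcome is assessed by CMR, scheduled only at month 1 and reachable by about 91% or more. Day-7 hs-CRP and in-hospital mortality are scarcely touched. Outcomes (2.8) gives MACE and repeat revascularization no time horizon, so a 12-month horizon is inferred from the end-point assessment listed at month 12. Still, MACE is the outcome on which the sample size rests, and month 12 is the only visit at which end-points are listed.

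A reader might go further and infer that almost no patient can reach month 12. That holds only if accrual is spread over most of the window; with 3 months of enrolment a third do, and mean follow-up is 11.3 of 12 months. A reader might also infer that most later echocardiograms would be missing. That fails at month 3 and largely at month 6, and is true of month 9 only under slow accrual.

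**Conclusion.** The point holds as a conflict between two stated schedules. A study window of 12 to 13 months leaves 0 to 31 days in which a patient can be enrolled and still complete month 12. This follows from the dates alone and needs no accrual assumption.

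How many patients are affected does depend on accrual. With even accrual in the widest window, between 8 of 100 (12 months of enrolment) and 33 of 100 (3 months) reach the end-point visit. The exposed items are the month-12 end-point assessment, post-discharge MACE and repeat revascularization, the month-12 echocardiogram and, if enrolment is slow, the month-9 one. The documents do not support extending the point to the CMR primary outcome. The stated 90% power plays no part in this finding.

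**What to change.** Reconcile Study timeline with Participation timeline. State the enrolment period separately and set the end of the study at the last enrolment plus 12 months. If October 2019 to October 2020 was meant as the enrolment period, say so and give the end as about October 2021.

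If the grant fixes the end date, state the last enrolment date and the common closing date. Then analyse post-discharge MACE and repeat revascularization as time-to-event, censored at closing, in place of simple proportions.

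Moving end-point assessment to month 1 is not a cheap way out. It changes the design, and patients enrolled in the last month of the window could not reach that visit either.

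The cost is small if only the dates are restated, though a later end may need the funder's agreement. With a fixed end date, the cost is shorter late follow-up for some patients and a changed analysis for late events.
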